## **10.3 Time to Progression and Survival**

Patients enrolled on this study who are confirmed to have a high grade glioma will be followed for all parameters until death. TTP is not a primary endpoint in this study but will be accessioned to derive hypotheses that may relate other data derived in this study with progression. Clinical and immunologic endpoints will be analyzed in all patients and statistical considerations powered based on enrollment of 20 patients. However, an analysis of patients stratified at enrollment based on complete resection or residual disease will be performed for hypothesis generation on the role of tumor burden on clinical and immunologic responses to CDX-110 vaccination and daclizumab.

Survival is not an endpoint in this study but will be accessioned to derive hypotheses that may relate data derived in this study with survival times. Patients will also be assigned a prognosis based on published recursive partitioning analysis of prognostic factors(Curran, Scott et al. 1993). Survival will be calculated from the date diagnostic tissue is first obtained.

Although not powered for survival analyses, the product limit estimator of Kaplan and Meier(Kaplan and Meier 1958) will be used to describe the distribution of survival time and TTP for both treatment groups, and the Cox proportional hazards model(Cox

1972) will be used to compare TTP and survival between the groups and with appropriate matched historical control groups. We would consider daclizumab worthy of further evaluation only if it did not significantly reduce TTP or overall survival relative to the control group and relative to the historical controls. Therefore, in the proposed study, we are interested in determining whether either treatment regimen is definitely worse than our best contemporaneous results at Duke University which are with the use of radiolabeled MABs delivered intratumorally. The most recent Phase II trial evaluating radiolabeled MABs at Duke in patients with newly-diagnosed GBM had a median survival of 79.4 weeks, and the lower limit of the 95% confidence interval was 61.4 weeks. Assuming that survival is exponential in this context, a median of 61.4 weeks translates into a 6-month survival of approximately 75%. Therefore if 6-month survival is not definitively <75%, there would remain interest in further development of the regimen proposed here. With 10 patients in each arm of our trial, one can conduct a test with  $\alpha=\beta=0.1$  to differentiate between a 6-month survival rate of 35% and 75%. That means that if the true 6-month survival rate were  $\leq 35\%$  there is <10% chance of concluding that the treatment regimen is worthy of pursuing with further investigation. Similarly, if the true 6-month survival rate were  $\geq 75\%$  or more there is  $\leq 10\%$  chance of rejecting the treatment. Other comparison groups that could be used include a historical control database, the recently published Phase III trial of the regimen of TMZ to be used in this trial, or our previous trial dataset using this vaccine approach which had median survivals (95% CI) of 14.7 (12.0, 17.4), 14.6 (10.9, 21.2), and >29.8 months, respectively. In addition, we will assess clinical efficacy by estimating the proportion of patients who survived longer than expected according to Curran's recursive partition analysis (Curran, Scott et al. 1993).

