#### **4.1.2 Disease Status**

The patient must have a histopathologic diagnosis of a high grade glioma (WHO Grade III or IV) as confirmed by the study pathologist, [name], or his designate. The patient must undergo leukapheresis for immunologic monitoring.

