### **7.4 Survival**

Survival data in the context of this Phase I/II trial will be interpreted with great care. Still there are a few studies in the literature that may be able to be compared to our study to some degree given that they have similar patient populations. For example, the carmustine polymer study(Westphal, Hilt et al. 2003) and the TMZ study(Stupp, Mason et al. 2005), both have a set of very similar inclusion and eligibility criteria.

In addition, the authors of this study are also aware of the benefit of recursive partitioning analysis of prognostic factors in the comparison of different treatment strategies for patients with MG(Curran, Scott et al. 1993; Lamborn, Chang et al. 2004). Comparison with these studies will allow us to compare the results of the current clinical trial to previously published trials of patients with similar prognostic features.

An intent-to-treat analysis will be conducted to compare the survival experience of patients identified to receive vaccine treatment upon completion of concurrent external beam radiation and temozolomide assuming there was no intervening disease progression to that experienced by a historical cohort of patients administered the same external beam radiation and temozolomide treatments(Stupp, Mason et al. 2005). Of particular interest is whether the survival experience of the two groups begins to diverge at the time that vaccine is administered 3-4 months after patient enrollment.

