### **10.3.1 Identification of Covariates**

Kaplan and Meier survival curves will be constructed and the Cox proportional hazards model will be used to identify continuous or discrete variables associated with TTP or survival from the immunologic measures and measures of the following predictors: serum EGFRvIII qPCR; serum anti-EGFRvIII titers; EGFRvIII-specific, IFN- $\gamma$  producing, CD8+/CD27-/CD28-/CD45RA-effector memory cells, 5-color positive cells, PEPvIII-KLH-specific tetramer-positive cells, and TReg number and function. Given the large number of predictors that will be examined relative to the overall sample size, it is recognized that these analyses will be exploratory. These analyses are conducted to generate hypotheses only and will need to be validated in additional patients or studies. Statistically, joint effects will also be explored, but are unlikely to have sufficient power to identify such interactions. Assuming that half the sample size of 24 patients are positive for a particular measure and that all have died, we will have 80% power for a logrank test conducted with  $\alpha=0.05$  to detect a survival hazard ratio of approximately 5.04 comparing patients with a positive and negative measure.

In addition, logistic regression and Fisher's exact Chi test will be used to explore whether the covariates outlined above predict the binary outcome of whether or not a patient survives longer than predicted according to Curran's (Curran, Scott et al. 1993) or Lamborn's (Lamborn, Chang et al. 2004) models. For example, for a continuous

predictor dichotomized at its median, given our patient sample size of 20, we will have 80% power to detect a difference in the “success” rate between 30% and 97% with  $\alpha=0.05$ .

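### The per-arm 6-month survival rule in protocol 10.3 runs from diagnosis, but patients join an arm about 13 to 20 weeks later, so most of the window is guaranteed survival and the rule is far too lenient

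*Protocol*

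**What the plan says.** Protocol 10.3 sets the time origin: "Survival will be calculated from the date diagnostic tissue is first obtained". It gives no other origin for the 6-month rule.

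The benchmark is an earlier trial in the same section: "The most recent Phase II trial evaluating radiolabeled MABs at Duke in patients with newly-diagnosed GBM had a median survival of 79.4 weeks". The rule does not use that median itself but its lower 95% confidence limit, 61.4 weeks. Assuming exponential survival, the section says that "a median of 61.4 weeks translates into a 6-month survival of approximately 75" per cent. The decision follows: "Therefore if 6-month survival is not definitively <75%, there would remain interest in further development of the regimen proposed here". With 10 patients per arm, the section claims a test of 35% against 75% with both error rates at 0.1.

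Sections 5.1.1 and 5.2.1 describe when the arms come into being. Patients first complete radiotherapy with temozolomide. Those who progress during radiation, cannot tolerate temozolomide or still depend on steroids are replaced. The remaining patients are randomised, and daclizumab or saline is given with vaccine #1. Sections 7.3 and 7.4 put vaccination 3 to 4 months after enrolment.

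**The concern.** A patient must be alive to be randomised and vaccinated, so no member of an arm can die during the first part of a window that opens at diagnosis. The 75% makes no allowance for this, because it is the survival of an exponential curve over a full 26 weeks at risk. Observed rate and benchmark therefore cover different periods at risk.

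At stake is the assurance in 10.3 that a regimen with a poor true rate has less than a 10% chance of being taken forward. If much of the window carries no risk, a large excess of deaths after vaccination can still give an acceptable 6-month figure.

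**Working it through.** **Reproducing the plan's figures.** Six months is taken as 26.09 weeks.

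- Benchmark: 0.5^(26.09/61.4) = 0.745, which agrees with the stated 75%.
- Test, exact binomial with n = 10: continuing if at least 6 are alive gives a 0.095 chance of passing at 35% and 0.922 at 75% (beta 0.078). A cut-off of 5 gives alpha 0.249, and a cut-off of 7 gives beta 0.224. Only 6 of 10 meets both stated limits. The protocol does not state the cut-off.

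The plan's arithmetic is sound. The difficulty is the time origin.

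**Time from diagnosis to vaccine #1** (5.1.2, 5.1.3, 5.2.1):

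- diagnosis to start of radiotherapy: 4 ± 2 weeks
- radiotherapy: 33 fractions at 5 per week = 6.6 weeks (under 7)
- break before the first temozolomide cycle: 3 ± 1 weeks
- start of that cycle to vaccine #1: 21 ± 2 days

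Mid-schedule: 4 + 6.6 + 3 + 3 = 16.6 weeks. Earliest: 2 + 6.6 + 2 + 19/7 = 13.3. Latest: 6 + 7 + 4 + 23/7 = 20.3. At mid-schedule, 26.09 − 16.6 = 9.5 weeks remain at risk on study treatment.

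**Effect on the rule.** Let h = ln 2 / 61.4 per week, L = weeks already survived at arm entry, and k = the multiple of the benchmark death rate after entry. Six-month survival is p = exp(−k·h·(26.09 − L)), and the pass probability is P(at least 6 of 10 alive) at p.

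| L (weeks) | p at k = 1 | p at k = 3 | Pass probability at k = 3 | k needed for 35% |
|---|---|---|---|---|
| 0 (clock starts at arm entry) | 0.745 | 0.413 | 0.19 | 3.6 |
| 13.0 (3 months) | 0.863 | 0.642 | 0.73 | 7.1 |
| 13.3 (earliest schedule) | 0.866 | 0.648 | 0.75 | 7.3 |
| 16.6 (mid-schedule) | 0.898 | 0.725 | 0.89 | 9.8 |
| 17.4 (4 months) | 0.907 | 0.745 | 0.92 | 10.7 |
| 20.3 (latest schedule) | 0.937 | 0.822 | 0.98 | 16.1 |

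**Sensitivity.** If entry is dated to the start of the first temozolomide cycle (4 + 6.6 + 3 = 13.6 weeks), a tripled rate passes with probability 0.76. With the 79.4-week median as benchmark, it passes with probability 0.87 to 0.97 for L from 13.0 to 17.4 weeks.

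**The case against.** **Weight.** Section 10.3 says survival is not an endpoint and that the study is not powered for it, and 7.4 promises cautious interpretation. This limits the importance of the point. It does not repair a rule that is given with explicit error rates and a development consequence.

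**All enrolled patients are analysed.** Section 10.1 keeps enrolled patients in the analysis even if they leave before treatment, and says this applies to the sections after it. Patients never randomised have no arm, however, so they cannot be among the 10 per arm. The two statements need reconciling.

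**Unknown benchmark origin.** The protocol does not say when the clock started in the radiolabelled-antibody trial. If its patients also entered late, part of the mismatch could be shared. This cannot be checked here.

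**Small sample.** Much of the insensitivity comes from n = 10 and the wide gap between 35% and 75%. Even counted from vaccine #1, a doubled death rate passes with probability 0.52, although that compares with 0.97 at mid-schedule under the present origin.

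**Stronger readings that the document does not support.** A reader might infer that every historical comparison is biased in favour of the vaccine. Section 7.4 describes an intent-to-treat comparison of "patients identified to receive vaccine treatment upon completion of concurrent external beam radiation and temozolomide assuming there was no intervening disease progression". That can mean a group selected after chemoradiation, or the treatment intended at enrolment. The question that follows, whether the curves begin to separate when vaccine is given, makes sense only if both curves start earlier. Section 7.3 also follows patients from first presentation where possible, and 10.3 calls for appropriately matched controls. The wording is ambiguous, which is not proof of bias.

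A reader might also infer that nothing would catch a harmful regimen. Section 10.3 also requires that daclizumab not significantly reduce time to progression or survival relative to the saline arm. Both arms share the same time before randomisation. Separate toxicity stopping rules stand in 5.3.2 and 10.2.

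Nor does the point extend to the covariate models in 10.3.1, which are labelled hypothesis-generating, or to the mix of WHO grades, whose effect cannot be sized from the document.

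**Conclusion.** The point holds for the per-arm 6-month rule in 10.3. Followed as written, the rule scores an arm at exactly the benchmark death rate at about 90% instead of 75%. It passes a tripled post-entry death rate with probability about 0.89 instead of 0.19, and needs about 10 times the benchmark rate, instead of 3.6 times, before true survival falls to 35%. A pass at a tripled rate is likely but not certain.

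These figures assume a constant hazard, a benchmark curve starting at time zero, the inferred 6-of-10 cut-off, and no deaths between diagnosis and arm entry among the patients counted. The last follows from the design if entry is vaccine #1.

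This is a fault in a secondary go/no-go statement. It should be corrected before the rule is used, but it leaves the primary T-reg analysis, the sample size and the randomised comparison untouched.

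**What to change.** 1. In 10.3, count the 6 months for the per-arm rule from randomisation or vaccine #1, name which, and write the cut-off down. Under the plan's exponential assumption the 75% and the n = 10 error rates are unchanged, because an exponential hazard is the same from any starting point.
2. State the time origin and entry point of the benchmark trial. If the exponential assumption is not relied on, take the benchmark from the same landmark.
3. Reconcile the 10-per-arm rule with the statement in 10.1 that all enrolled patients are analysed.
4. In 7.3 and 7.4, state which patients enter the historical comparison. If only those free of progression after radiotherapy and temozolomide do, use historical patients from that same landmark.

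The cost is wording, with no added patients, visits or assays. Step 4 may require historical data that identify progression status at the end of chemoradiation. The rule will remain coarse at 10 patients per arm, and the text should say so.

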### **10.3.1 Identification of Covariates**

Kaplan and Meier survival curves will be constructed and the Cox proportional hazards model will be used to identify continuous or discrete variables associated with TTP or survival from the immunologic measures and measures of the following predictors: serum EGFRvIII qPCR; serum anti-EGFRvIII titers; EGFRvIII-specific, IFN- $\gamma$  producing, CD8+/CD27-/CD28-/CD45RA-effector memory cells, 5-color positive cells, PEPvIII-KLH-specific tetramer-positive cells, and TReg number and function. Given the large number of predictors that will be examined relative to the overall sample size, it is recognized that these analyses will be exploratory. These analyses are conducted to generate hypotheses only and will need to be validated in additional patients or studies. Statistically, joint effects will also be explored, but are unlikely to have sufficient power to identify such interactions. Assuming that half the sample size of 24 patients are positive for a particular measure and that all have died, we will have 80% power for a logrank test conducted with  $\alpha=0.05$  to detect a survival hazard ratio of approximately 5.04 comparing patients with a positive and negative measure.

In addition, logistic regression and Fisher's exact Chi test will be used to explore whether the covariates outlined above predict the binary outcome of whether or not a patient survives longer than predicted according to Curran's (Curran, Scott et al. 1993) or Lamborn's (Lamborn, Chang et al. 2004) models. For example, for a continuous

predictor dichotomized at its median, given our patient sample size of 20, we will have 80% power to detect a difference in the “success” rate between 30% and 97% with  $\alpha=0.05$ .

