Patients will receive TMZ which will be delivered every 4 weeks. Therefore, in addition to the concurrent TMZ (75 mg/m^2/d) given with radiation, a total of 6 additional cycles of TMZ (100 mg/m^2/days 1-21) will be given. While standard dose 21-day TMZ treatment at a target dose of 100 mg/m^2/day is recommended, TMZ regimen may be adjusted at the discretion of the treating neuro-oncologist. Vaccine will always be given on day  $21 \pm 2$  of each 28 day TMZ cycle. Subsequent vaccines will be given on day  $21 \pm 2$  of each of the five remaining TMZ cycles. Cohort #2 will receive subsequent vaccinations along with daclizumab (1 mg/Kg) on day  $21 \pm 2$  for first 3 cycles. Vaccines will then continue monthly until progression. An additional leukapheresis will be required for any patients who have a positive DTH skin test for PEPvIII for immunologic monitoring.

If the TMZ cycles are completed without progression, monitoring will continue until clinical or radiographic progression without any additional prescribed antitumor therapy. During that time period, patients will be monitored clinically with routine physical and neurologic examinations and MMSE testing at every visit and with a contrasted-enhanced CT or MRI every  $8 \pm 4$  weeks. Peripheral blood will be obtained as outlined in the study flow sheet below for sub-clinical autoimmunity and immunologic monitoring.

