### **6.2.4 During and After Immunizations**

- Clinical evaluations with each vaccine or leukapheresis will include a general physical, neurologic, and ophthalmologic examination, KPS, and MMSE.
- Radiographic evaluations consisting of a contrast enhanced brain CT or MRI scan will be obtained every 8  $\pm$  4 weeks.
- Blood will be obtained for T4/T8 ratio (Lab Code 2500202), ABC (Lab Code 2010200) with manual differential (Lab Code 2000640), serum for PEPvIII-KLH ELISA ([name] Lab), and 10 yellow ACD (9 mL), 3 red (9 mL), and 1 purple (3 mL) tubes for Immunologic Monitoring *prior* to vaccination #1 and with each vaccination after vaccination #3. Blood will also be obtained for

sub-clinical autoimmunity prior to vaccine # 1 and every 4 months after vaccine # 3. Estimated volume of blood for these tests is 120 cc.

- During TMZ cycles, ABC (Lab Code 2010200) with manual differential (Lab Code 2000640) will be monitored at the time of vaccination (day  $21 \pm 2$ ) and before the next TMZ dosing of each 4 week cycle.
- DTH testing will occur with the fourth vaccination (SOP-JHS-HDC-CL-014 “Delayed Type Hypersensitivity Testing Procedure”). Results will be read and recorded on the appropriate form (FORM-JHS-HDC-CL-014C “Delayed Type Hypersensitivity Testing Form”)  $48 \pm 24$  hours later. An additional leukapheresis will be required for any patients who have a positive DTH skin test for PEPvIII for immunologic monitoring.

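### Section 10.3.1 relates post-vaccination immune measures to TTP and survival with no landmark or time-dependent coding, so being classed positive depends partly on how long a patient stays progression-free

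*Protocol*

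**What the plan says.** **Analysis.** Protocol section 10.3.1 announces Kaplan-Meier curves and says the "Cox proportional hazards model will be used to identify continuous or discrete variables associated with TTP or survival from the immunologic measures". The predictors listed include anti-EGFRvIII titers, EGFRvIII-specific T cells, EGFRvIII qPCR, and TReg number and function. The section's power statement is for a logrank test "comparing patients with a positive and negative measure". The same covariates then go into logistic regression and Fisher's test of whether a patient outlives the prediction of a published prognostic model. No draw, landmark or time-dependent covariate is mentioned.

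**Time origin.** Section 10.3: "Survival will be calculated from the date diagnostic tissue is first obtained". No origin is stated outright for TTP. Section 7.3 only says patients are followed from initial presentation where possible, and puts vaccine administration 3–4 months after enrollment.

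**When the measures are taken.** Section 6.2.4 schedules the full monitoring blood before vaccination #1 "and with each vaccination after vaccination #3". Section 5.2.1: "Vaccines will then continue monthly until progression". The flow sheet (section 11) adds a monitoring draw at progression and smaller tubes before vaccines #2 and #3. Section 8.12 takes qPCR blood before each immunization.

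**Who is analysed.** Section 10.1 keeps all enrolled patients in its own analysis and in those that follow it, including patients taken off study before any treatment.

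**Status.** Section 10.3.1 calls these analyses exploratory, because the predictors are many relative to the sample size, and says they need validation.

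**The concern.** Kaplan-Meier, logrank, logistic and Fisher analyses each need one fixed value per patient, and a fixed-label comparison is valid only if membership is settled when the clock starts. Here the clock for survival starts at diagnosis, months before any post-vaccine sample, and the number of monthly samples is set by time to progression. The outcome helps to decide who is in the positive group, so positive patients tend to look better even when the immune measure has no bearing on outcome.

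The exploratory label answers a different problem. It warns about many predictors and few patients, which is chance error. Guarantee-time bias is systematic and favours the positive group each time. At stake is which immune response is carried forward as a correlate of benefit: section 8 expects these assays to inform the design of later CDX-110 trials.

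**Working it through.** **1. The plan's own figure.** The scenario in section 10.3.1 reads: "Assuming that half the sample size of 24 patients are positive for a particular measure and that all have died". The claim is that a logrank test at α = 0.05 can then, with 80% power, "detect a survival hazard ratio of approximately 5.04 comparing patients with a positive and negative measure". Detectable HR by Schoenfeld, two-sided: exp[(1.96 + 0.842)/√(0.25·D)].
- D = 24 deaths: exp(2.802/2.449) = 3.14.
- D = 12 deaths: exp(2.802/1.732) = 5.04.

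The stated figure matches 12 deaths, not 24; with 24 deaths an HR of 5.04 would have 97.7% power. That is a separate slip. What matters here is that the calculation treats each patient as carrying one fixed positive or negative label.

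**2. Why the label depends on TTP.** Take draws from 5.5 months after diagnosis, then monthly until progression. A patient progressing at 6.9 months has 2 draws; one progressing at 12.1 months has 7 (both times are TTP medians quoted in section 3.4.3). With an illustrative 9.4% chance of turning positive at each draw, the same for everyone:
- 2 draws: 1 − 0.906² = 18% ever positive.
- 7 draws: 1 − 0.906⁷ = 50% ever positive.

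The biology is identical and only the time at risk differs.

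**3. False-positive rates with no true association.** Two simulations, each with a two-sided 5% logrank test and 6-month median post-progression survival (assumed). Everyone is progression-free to vaccine #1, about 3.8 months (16.6 weeks) after diagnosis, and TTP is exponential thereafter.
- *Model A* (N = 20): median TTP 6.9 or 12.1 months; median time to response 2, 4 or 8 months (assumed).
- *Model B* (N = 20 and 24): median TTP 7.1 or 12.1 months; 38%, 50% or 62% ever positive (38% and 62% are response rates in section 3.4.3).

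| Rule for positive | Outcome | Model A, N=20 | Model B, N=20 | Model B, N=24 |
|---|---|---|---|---|
| Any draw before progression | TTP | 51–98% | 73–100% | 81–100% |
| Any draw before progression | Survival | 13–61% | 24–64% | 28–70% |
| Any draw, progression draw added | TTP | 45–93% | not run | not run |
| Any draw, progression draw added | Survival | 12–57% | not run | not run |
| Vaccine #4 draw only, unreached counted negative | TTP | 2–18% | 9–23% | 11–26% |
| Vaccine #4 draw only, unreached excluded | TTP | 7–9% | 6–8% | 6–7% |
| Time-dependent covariate | TTP | not run | 5–7% | 5–6% |
| Random label (baseline) | TTP | not run | 6–8% | 6–7% |

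A repeat of Model A with unreached patients excluded gave 7–11%. With unreached patients counted negative, survival stayed at 6–8% in Model A, so under that rule the excess is confined to TTP.

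The 2% low end arises where almost nobody is positive yet. With median TTP 6.9 and response median 8 months from vaccine #1, the expected number positive at 5.5 months is 20 × 2^(−1.7/3.1) × (1 − 2^(−1.7/8)) = 20 × 0.684 × 0.137 ≈ 1.9, too few for the test to reject often.

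**4. Direction.** In Model B at N = 24, median TTP 12.1 months and 50% ever positive, the median apparent HR is 0.18 for TTP and 0.33 for survival, although the true value is 1. With time-dependent coding of the same data the TTP HR is 0.98.

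**The case against.** The strongest reply is that section 10.3.1 prescribes no biased rule. It names no draw, a Cox model can take time-dependent covariates, and the positive/negative split appears only in a power illustration. The choice of sample could be left to an analysis plan that is not shown. This stands as far as the draw is concerned. A reader might infer that the protocol classes a patient as positive if any draw, or the highest titer, is positive, and so quote only the largest error rates. The text contains no such rule.

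A reader might also infer that early progressors are negative by default because they are never sampled. The flow sheet contradicts that: there is a draw at progression, smaller draws before vaccines #2 and #3, and qPCR blood before each immunization. Adding the progression draw lowers the rates only modestly, however.

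Three further limits hold. Pre-vaccine measures are unaffected. Monthly TReg function assays are not established, since section 8.2 describes the assay on leukapheresis samples and section 5.1.4 repeats leukapheresis only in responders. The diagnosis origin is stated for survival alone.

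What remains is in the protocol itself. The Kaplan-Meier, logistic and Fisher analyses need a fixed value per patient, and section 10.1 brings in patients who can have no post-vaccine value. The choice that removes the bias (one early draw, unreached patients left out) conflicts with section 10.1 as written.

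**Conclusion.** The point holds in a limited form. As written, section 10.3.1 is open to guarantee-time bias for predictors measured after vaccination, in the direction of making immune response look favourable. Its size cannot be fixed from the protocol, because the defining draw is not named:
- Any draw counts: about 45–98% false positives for TTP and 12–61% for survival at N = 20 in Model A, the lower ends including the progression draw; Model B reaches 100% and 64%.
- Vaccine #4 draw only, unreached patients negative: about 2–26% for TTP (the top at N = 24).
- Vaccine #4 draw only, unreached patients excluded: about 6–10%, essentially the error of a small-sample logrank test.

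These figures rest on exponential times, the assumed 6-month post-progression median and the assumed response rates. Severity is minor to moderate: neither TTP nor survival is a primary endpoint, the analysis generates hypotheses only, and no treatment comparison or stopping rule depends on it.

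**What to change.** Amend section 10.3.1 for predictors measured after vaccination:
- Classify each patient at the vaccine #4 draw, among those alive and progression-free at that draw, and count TTP and survival from its date.
- Let later values enter only as time-dependent covariates in the Cox model. This was checked for TTP only. For survival the landmark analysis should lead, because the serial draws stop at progression.
- Use the same landmark set for the logistic and Fisher analyses.
- Exempt this analysis from the all-enrolled rule in section 10.1.
- State the time origin for TTP, and say which predictors (TReg function in particular) have a vaccine #4 value. Baseline predictors can stay as they are.

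This changes wording only and needs no new data. The cost is that patients who progress or die before vaccine #4 leave this exploratory analysis, which shrinks an already small sample.
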